## Background

Acute Achilles tendon rupture is an increasingly common injury during both sports and recreational activities [1]. Numerous studies investigating operative versus non-operative treatment with a focus on re-rupture rate and complications related to the treatment have been performed. Overall, non-operative treatment results in a higher re-rupture rate, which is argued to be acceptable due to the lower rate of serious complications such as sural nerve damage and deep infections [2–6]. As a consequence, recent studies have focused on refining non-operative treatment of acute Achilles tendon ruptures [7–9]. Simultaneously, standard treatment of acute Achilles tendon rupture has shifted from operative to non-operative in many Scandinavian departments [1, 10], though the impact on functional outcome of this change toward non-operative treatment is not yet clear [11, 12].

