#### Analysis of endpoints

Demographic parameters will be presented for each treatment group with mean and standard deviation (SD) or median and interquartile range (IQR) for continuous parameters and frequencies and percentages for categorical parameters.

Difference in Heel-rise work test will be tested by *t*-test or, if data can’t be assumed to be normally distributed, Wilcoxon sum rank test. Test will be made for the comparison individual vs operative treatment and individual vs non-operative treatment. To account for possible confounders, a linear regression will also be fitted for each comparison. Confounders include, but are not limited to, sex, age, BMI, and ATRS pre-injury; the confounding effect of these variables will be evaluated in the model by including and removing the variable and evaluating the change between the treatment group estimates.

Differences in severe complications (yes/no) between individual and operative treatment will be tested by chi-square test or, if the amount of expected observations for a single combination is less than 5, Fishers exact test. Additionally, the test will be adjusted for possible confounders in a logistic regression model; possible confounders and evaluation of these will be done as described in the Heel-rise work test models. Similar tests and models are made for the comparison of individual and non-operative treatments. Differences between individual and operative treatment and individual and non-operative treatment for all other secondary outcomes will be tested by *t*-test or Wilcoxon sum rank test.

All analysis will be done as intention-to-treat (ITT), that is, each patient is analyzed according to the treatment group they are randomized to. The results will therefore be interpreted as the effect of offering the patient the specific treatment options, regardless of if they complete them or not. Missing data will be imputed by multiple imputation, with imputation models based on available variables believed to be predictive of the missing measures. Additionally, the analysis for the primary outcome will be conducted as per protocol analysis, with per protocol defined as patients complying with the assigned protocol.

No interim analyses will be done.

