### Safety

#### Risks and side effects

All participants in the study are at risk of developing pressure wounds from the functional brace and cast and a small risk of developing adhesion of the tendon to the skin. For participants receiving non-operative treatment there is a higher risk of re-rupture and an expected relatively higher risk of elongation of the injured Achilles tendon and inferior muscular force in the plantar flexion over the ankle joint compared to the patients receiving operative treatment. For the participants receiving operative treatment there is a risk of infection in the operative wound and temporary or permanent damage to the sural nerve.

The only possible need of modifying the allocated intervention for a given trial participant is if a participant treated non-operatively has insufficient healing after 12–16 weeks after injury or experiences a trauma re-injuring the tendon during the healing phase. In these situations, surgery is most often needed.

All participants are covered by the hospitals insurance during the treatment period.

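### The adjusted logistic model for severe complications has no provision for sparse events, although the unadjusted test of the same outcome does

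*Protocol article*

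**What the plan says.** All of this is in the protocol article under Analysis of endpoints.

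- Unadjusted test: "Differences in severe complications (yes/no) between individual and operative treatment will be tested by chi-square test".
- Switch of that unadjusted test when the table is sparse: "if the amount of expected observations for a single combination is less than 5, Fishers exact test".
- Adjusted analysis: "Additionally, the test will be adjusted for possible confounders in a logistic regression model". No minimum event count, penalised or exact estimator, or type of test is attached.
- Covariates: "possible confounders and evaluation of these will be done as described in the Heel-rise work test models". For the heel-rise models, "Confounders include, but are not limited to, sex, age, BMI, and ATRS pre-injury". Each candidate is added and removed, and its effect is judged by how far the treatment estimate moves.
- Second comparison: "Similar tests and models are made for the comparison of individual and non-operative treatments".

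The article gives no expected rate for severe complications and does not define which events count as severe.

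**The concern.** The authors foresee that severe complications may be rare enough for chi-square to fail, and they provide for it. The provision stops at the unadjusted test. The regression that follows depends more on the event count than the test does, yet it is prescribed whatever that count turns out to be.

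Two things can go wrong. With few events in both arms, the adjusted odds ratio is unstable and moves when irrelevant covariates are added, so the change-in-estimate rule picks up noise. With no events in one arm, the maximum-likelihood odds ratio does not exist. Software then typically prints a very large coefficient with a huge standard error, and the rule has no treatment estimate to compare. At stake is a readable adjusted result for the main safety comparison.

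**Working it through.** **The article's own figure.** Under Sample size, 2 × (1.96 + 1.281)² × 20² / 10² = 84.03, which reproduces the stated 84 per group (100 with dropout). It concerns the primary outcome only. No figure is given for complications, so the rates below are assumptions.

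**Step 1: what the Fisher condition implies.** Allocation is 1:1:1, so two compared arms are about equal. With T events in total, the expected number per arm is T/2. T/2 < 5 means T ≤ 9.

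**Step 2: events per coefficient.** Treatment plus the four named candidates is 5 slopes, so at most 9/5 = 1.8 events per coefficient if all are kept. With treatment and one covariate it is at most 9/2 = 4.5.

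**Step 3: one empty arm, 6/100 versus 0/100** (expected count 3, so Fisher applies).

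- Fisher's exact test: p = 0.029.
- Maximum-likelihood logistic fit, treatment only: log odds ratio about 21.8 where the iterations stopped, standard error about 13,100, Wald p = 0.999. With simulated covariates added: 22.8, about 20,300 and 0.999.
- Likelihood-ratio test, treatment only: the log-likelihood is −22.697 with separate rates (the empty arm contributes 0) and −26.948 with a common rate of 6/200. The statistic is 2 × (26.948 − 22.697) = 8.50 on 1 degree of freedom, p = 0.0035.
- Adding 0.5 to each cell, which is the Firth estimate for a 2×2 table: (6.5/94.5)/(0.5/100.5) = 13.8. It is finite, with an approximate Wald 95% interval of 0.77 to 249.

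In the tables tried with 0 events in one arm and up to 12 in the other, at 84 and 100 per arm, the fitted coefficient diverged in the same way.

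**Step 4: few events, neither arm empty.** For 7 versus 1 of 100 the odds ratio is (7/93)/(1/99) = 7.5, with Wald p = 0.063 and Fisher p = 0.065, so the unadjusted results agree. The covariate rule still behaves badly. With four pure-noise covariates (500 simulated trials per table, 100 per arm), adding all four moved the treatment odds ratio by more than 10% in 41% of runs for 1 v 7, 41% for 2 v 6 and 33% for 3 v 6. The 10% threshold is an assumption, since the article names none.

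**Step 5: how often an arm is empty.** Let X and Y be binomial event counts with n per arm and assumed rates p₁ and p₂. The quantity is P(exactly one of X, Y is 0, and 1 ≤ X+Y ≤ 9) / P(1 ≤ X+Y ≤ 9).

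| Assumed rates | n = 84 per arm | n = 100 per arm |
|---|---|---|
| 4% / 4% | 7% | 5% |
| 6% / 2% | 21% | 17% |
| 5% / 1% | 44% | 39% |

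The result depends mainly on the lower rate. The chance of no events in 100 patients is 0.99¹⁰⁰ = 37% at 1% and 0.98¹⁰⁰ = 13% at 2%.

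**The case against.** Several stronger readings are tempting, and the article does not support them.

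- *A reader might infer that the Fisher condition itself produces an infinite odds ratio.* It does not. The condition means at most 9 events; the failure needs an empty arm or separation by a covariate. At the assumed rates most trials meeting the condition have events in both arms, and simulated bias there was small.
- *A reader might infer that the non-operative arm will have about no events.* The article does say that "For the participants receiving operative treatment there is a risk of infection in the operative wound and temporary or permanent damage to the sural nerve", and Background credits non-operative treatment with a "lower rate of serious complications such as sural nerve damage and deep infections". But the model is for one composite, not for single surgical harms. The article also expects more re-ruptures without surgery, and under intention-to-treat any complication of later surgery stays in the non-operative arm. Whether re-rupture counts as severe is not stated, so an empty arm is possible but is not the article's expectation.
- *A reader might infer that the planned p-value will be near 1.* That holds for a Wald test only, and no test is named. The likelihood-ratio test on the same data gives a small p-value. It does not rescue the confounder rule, which works on the coefficient. The planned multiple imputation is also usually pooled from coefficients and standard errors, which is Wald-type inference.
- *A reader might infer that a harm would be missed or misreported.* Chi-square or Fisher is reported in any case, and a standard error in the thousands is easy to recognise as failed estimation.

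The four covariates are candidates, not a fixed model, so 1.8 events per coefficient is the case with all four kept. Finally, the choice of estimator is often left to a statistical analysis plan, and one not shown may already settle it. What remains is that the article itself sets a sparse-data rule and applies it to only half of the analysis of this outcome.

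**Conclusion.** The point holds in limited form. The article recognises sparse complication data, protects the unadjusted test, and leaves the adjusted logistic model for both comparisons without protection. Under the Fisher condition the adjusted estimate and the change-in-estimate rule are unreliable. With an empty arm there is no finite maximum-likelihood estimate and the rule cannot be applied. How often that happens rests on assumed rates: roughly one in twenty trials meeting the condition at 4%/4%, and about two in five at 5%/1%. The contradiction with Fisher further assumes Wald inference.

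The consequence is an adjusted safety result that could be uninterpretable or at odds with the exact test beside it, not a lost signal. This is a minor point on a secondary outcome. The primary analysis and sample size are unaffected, and no question of clinical management arises.

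**What to change.** Add two sentences under Analysis of endpoints, or confirm that the statistical analysis plan contains them:

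1. When the condition for Fisher's exact test is met, the adjusted analysis of severe complications uses Firth penalised logistic regression with profile-likelihood confidence intervals. It uses a small covariate set named in advance, with no selection by change in the estimate.
2. Fisher's test is accompanied by the risk difference with a score or exact confidence interval.

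Profile-likelihood intervals matter here because the Wald interval in the worked example (0.77 to 249) includes 1 while Fisher's p-value is 0.029. The adjusted model need not be dropped.

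The cost is slightly more analysis work and an odds ratio shrunk towards 1. No new data are needed.

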**Methods/design:**

This study is conducted as a multicenter, three-armed randomized controlled trial. Participants are included from four hospitals in Denmark and randomized 1:1:1 to one of three parallel groups: 1) Intervention group—participants are treated according to an individualized treatment algorithm; 2) Control group A—participants are treated non-operatively; 3) Control group B—participants are treated operatively. The individualized treatment algorithm for the intervention group is based on an ultrasonographic examination; tendon overlap and elongation below 7% is to be treated non-operatively, while no tendon overlap and/or elongation above 7% will be treated operatively. Over a period of 3 years, 300 participants will be included. The primary outcome is the heel-rise work test at 12 months post-injury. Secondary outcomes are tendon elongation, the Achilles tendon Total Rupture Score (ATRS), the rate of re-ruptures, and other complications. The primary analysis will be conducted as an intention-to-treat analysis.

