### Secondary outcome measures

The secondary outcome measures are listed below (the timing of the assessments is shown in Fig. 1).
Copenhagen Achilles Length Measure (CALM) [19] is an ultrasonographic measurement of tendon elongation. It comprises two measurements (Fig. 2): the total length of the Achilles tendon (free tendon and fascia) and the free length of the Achilles tendon. The measurements are preformed the same way; they have the same distal landmark but the proximal landmark differs. CALM has shown good reliability and is recommended over other measurements of elongation [17, 20, 21]. The measure is performed as described by Barfod et al. but with the feet of the patient (laying in the prone position) hanging free of the table instead of with 10° degrees of plantar flexion in the ankle joints as originally described [16, 21]. Landmarks are identified and marked on the skin. The distal landmark is the posterior and most superior part of the calcaneus in the midline, which on sagittal ultrasound examination is identified as the point where the cortical bone and its underlying shadow end. The proximal landmark for the total length of the Achilles tendon is the distal tip of the medial gastrocnemius head, which on sagittal ultrasound examination is recognized as the point where the most distal muscular fibers are inserted into the deep crural fascia. The proximal landmark for the free length of the Achilles tendon is the distal tip of the soleus muscle, which is defined at the point where the most distal muscular fibers insert into the Achilles tendon. The distance between these two points on the un-injured leg defines the total length of the Achilles tendon and the free length of the Achilles tendon, respectively. The differences between the non-injured and the injured leg are defined as tendon elongation. At inclusion only the total Achilles tendon length is measured for both legs. The examination of both the total and the free part of the tendon of both the injured and un-injured leg is performed at 6- and 12-month follow-up. The position of the feet also differs between inclusion and follow-up. During inclusion, the originally described position of the feet is used (10° of plantar flexion in the ankle joints) but during the 6- and 12-month follow-up, the feet hang free of the table.Heel-rise work test: The test is conducted as described for the primary endpoint and conducted as a secondary endpoint at 6 months.Achilles tendon resting angle (ATRA) [22]: ATRA is an indirect measurement of tendon elongation. The patient lies flat in the prone position on the examination bed. The knee is flexed at 90 degrees and the ankle sits in a relaxed position. The ATRA is determined as the angle between the longitudinal axis of corpus of the fibula and the longitudinal axis of corpus of the fifth metatarsus. ATRA is determined for both the injured and the uninjured leg. The difference between the healthy and the injured leg is evaluated. ATRA has shown excellent reliability [22, 23].Complications: Incidence rates of the commonly known complications and adverse events such as infection, re-rupture, permanent sural nerve dysfunction, deep venous thrombosis, adhesions, and pain at the scar are noted. Attention is also paid to unknown complications in relation to the treatments.Achilles tendon Total Rupture Score (ATRS) [24]: Patients fill out the ATRS questionnaire at inclusion and after 6 and 12 months in connection with the follow-up visits in the outpatient clinic. ATRS is a patient-reported outcome measure developed to assess symptoms and physical activity after treatment for acute Achilles tendon rupture. The Danish version was found to have good validity and be reliable to use for comparison on the group level [25].Tegner Activity Scale: A scale that aims to provide a standardized method of grading work and sporting activities. Tegner activity scale is a graduated list of activities of daily living, recreation, and competitive sports. The patient is asked to select the level of participation that best describes their level of activity at inclusion and at 6 and 12 months after rupture and before injury [26].Calf circumference: The patient sits on an examination bed with legs hanging down. The circumference of the calf is measured using a measuring tape (13 cm under apex patella).MRI: MRI of the calf is performed after 1 year for the first 60 patients included at Copenhagen University Hospital Amager-Hvidovre. MRI will be conducted to obtain a deeper understanding of changes to the different structures in the muscle–tendon complex during the first year after rupture. The MRI will be conducted at Copenhagen University Hospital Amager-Hvidovre in an Acanto 1.5 T scanner. Both lower legs will be scanned.Gait analysis: Gait analysis is performed after 6 and 12 months for the first 60 patients included at Copenhagen University Hospital Amager-Hvidovre. The gait analysis will be conducted at the Gait Laboratory, Copenhagen University Hospital Amager-Hvidovre. Twenty-two reflective markers are placed on the patient’s skin with tape on specific anatomical locations, as described by Speedtsberg et al. [27]. The participants are instructed to walk barefoot at a self-selected speed on a 10-m level walkway. The reflective markers are filmed by eight infrared cameras, whereby the joint angles during gait are measured. In combination with the ground reaction forces from two force plates embedded in the floor, the joint moments and powers will be calculated.

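### As written, any yes/no complication not labelled severe, possibly including re-rupture, is compared by t-test or Wilcoxon; the choice matters only when events are sparse

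*Protocol article*

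**What the plan says.** The Analysis of endpoints section of the protocol article sets two rules for secondary outcomes.

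- **First rule.** It opens with "Differences in severe complications (yes/no) between individual and operative treatment". These are compared by chi-square test, or by Fisher's exact test if an expected cell count is below 5, and a logistic regression adjusts for confounders. The same is planned for individualized against non-operative treatment.
- **Second rule.** Differences between individualized and operative treatment, and between "individual and non-operative treatment for all other secondary outcomes will be tested by" t-test or Wilcoxon rank sum test.

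The binary outcomes are named elsewhere. The abstract's list of secondary outcomes ends with "the rate of re-ruptures, and other complications". The Complications item under Secondary outcome measures covers "Incidence rates of the commonly known complications and adverse events such as infection, re-rupture, permanent sural nerve dysfunction" and goes on to name thrombosis, adhesions and scar pain. Neither place grades the events by severity.

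**The concern.** The second rule takes in whatever the first leaves out, and the first names only severe complications. A yes/no event that is not called severe therefore falls to a test of means or ranks.

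The article does not say which events are severe. Three nearby notions point in different directions for re-rupture:

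- Background speaks of a "lower rate of serious complications such as sural nerve damage and deep infections" and sets this against re-rupture, so re-rupture lies outside that group.
- Adverse events puts re-rupture among the events given special attention.
- Critical adverse events defines its term by consequences such as hospitalization or permanent disability, so a re-rupture might or might not qualify.

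None of the three is tied to the analysis term. Re-rupture against surgical complications is the main harm trade-off between the arms (Background; Risks and side effects). A label chosen later would decide which test re-rupture gets and whether the adjusted logistic model is run for it. A comparison of means or ranks is also not framed as the risk comparison that readers need.

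**Working it through.** **Inputs.** From Sample size: 100 randomized per arm, 84 per arm before the dropout allowance, significance level 0.05 two-sided (1.96). From Analysis of endpoints: Fisher if an expected count is below 5, otherwise chi-square. The article gives no complication rates, so all event counts and rates below are assumptions.

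**Step 1, the article's own figure.** N = 2 × (1.96 + 1.281)² × 20² / 10² = 84.03, which matches the stated 84. It concerns the primary outcome and is unaffected by this point.

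**Step 2, when the article's rule uses Fisher.** With two equal arms and m events in total, the smallest expected count is m/2. It is below 5 exactly when m < 10.

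**Step 3, one case by hand: 0 v 5 events, 100 per arm.**

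- t-test: the difference is 0.05. Pooled variance = 100 × 0.05 × 0.95 / 198 = 0.0240. Standard error = √(0.0240 × 2/100) = 0.0219. t = 2.28 on 198 degrees of freedom, p = 0.0235.
- Fisher, two-sided: 2 × C(100,5) / C(200,5) = 0.0594.

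**Step 4, other counts, 100 per arm.**

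| Events | t-test | Wilcoxon | Article's rule for yes/no data |
|---|---|---|---|
| 0 v 4 | 0.044 | 0.044 | Fisher 0.121 |
| 0 v 5 | 0.024 | 0.024 | Fisher 0.059 |
| 0 v 6 | 0.013 | 0.013 | Fisher 0.029 |
| 1 v 6 | 0.055 | 0.055 | Fisher 0.118 |
| 1 v 7 | 0.030 | 0.031 | Fisher 0.065 |
| 1 v 8 | 0.017 | 0.017 | Fisher 0.035 |
| 3 v 8 | 0.122 | 0.122 | chi-square 0.121 |
| 3 v 10 | 0.045 | 0.045 | chi-square 0.045 |
| 5 v 14 | 0.030 | 0.030 | chi-square 0.030 |

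The conclusion at 0.05 changes for 0 v 4, 0 v 5 and 1 v 7. Running through every pair with fewer than 10 events in total finds no others. With 84 per arm the same three pairs change (0 v 5: 0.023 / 0.024 v 0.059). From 10 events upward the tests practically agree, because on 0/1 data the t-test and the Wilcoxon test nearly equal the uncorrected chi-square test.

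**Step 5, how often this happens.** Exact binomial enumeration, 100 per arm, rates assumed:

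| True rates | t-test rejects | Article's rule rejects | Conclusions differ |
|---|---|---|---|
| 2% v 2% | 4.0% | 0.5% | 3.5% |
| 3% v 3% | 4.5% | 1.3% | 3.2% |
| 5% v 5% | 4.4% | 3.3% | 1.1% |
| 10% v 10% | 5.2% | 5.2% | about 0% |
| 1% v 6% | 49% | 33% | 16% |
| 2% v 8% | 49% | 43% | 6% |
| 3% v 10% | 53% | 51% | 1.6% |
| 5% v 15% | 68% | 68% | about 0% |

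Wilcoxon rejection rates equal those of the t-test to the precision shown.

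**The case against.** The best defence is that Complications is a single item in the list of secondary outcomes, and that the other items are mainly measurements, scores or ordinal scales. All other secondary outcomes could then mean everything except complications. Primary outcome measure supports this in part, since it allows results to be summarized as percentages or proportions. The reading is plausible as intent, but the text does not carry it: the first rule names only severe complications, and the abstract lists the re-rupture rate separately.

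A second defence is that the make-up of severe complications may be set out in the full protocol or analysis plan, which are not shown. That stands, and the missing definition alone is not a fault of a condensed article. It matters here only because a rule that the article does state depends on it.

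A third is that much of the gap is Fisher's conservatism with few events rather than a failing t-test. That also stands: the t-test rejected in 4.0% to 5.2% of null cases.

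A reader might go further and infer that re-rupture will certainly be t-tested, that false-positive findings will multiply, or that the adjusted logistic model must be replaced because events will be too few. The documents support none of these. Re-rupture may yet be counted as severe, the error rate is close to nominal, and no event rates are given from which to judge the logistic model.

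**Conclusion.** The point holds as a fault in a stated rule. The wording gives a test for means or ranks to any yes/no complication outside an undefined severe category, and re-rupture may be among them.

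Its size is limited. Significance can turn on the label only with fewer than 10 events across two equal arms, and there only for a few patterns of counts. At assumed rates of 1% v 6% the two routes disagree in 16% of trials, and by 5% v 15% in practically none. Type I error is not materially inflated. The outcomes are secondary, and the sample size and primary analysis are untouched. What is at stake is that the test for a key harm should not hang on a later label. These figures rest on 100 patients per arm and on assumed event rates.

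**What to change.** Amend Analysis of endpoints, or the analysis plan, as follows:

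1. Restrict t-test and Wilcoxon test to continuous and ordinal secondary outcomes.
2. Analyse re-rupture and every other yes/no complication by the chi-square/Fisher rule already in the text. Report counts, percentages and a risk difference with 95% CI for each of the two comparisons.
3. State before analysis which events count as severe, so that the label defines an endpoint and no longer selects the test.

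The cost is wording only, with no new data and no change in sample size. One small downside is that Fisher's test is conservative when events are few, so some p-values will be less favourable than under the t-test. The risk difference and its interval keep the size of the effect visible.
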